#### Interim analyses {21b}

Not applicable.

#### Methods for additional analyses (e.g., subgroup analyses) {20b}

The efficacy analysis will be based on the intention-to-treat analysis, which will be conducted in all patients who have been randomized and used drugs. There will be no pre-defined subgroup analysis. If unusual or unexpected results occur, then post-hoc subgroup analyses may be used.

#### Methods in analysis to handle protocol non-adherence and any statistical methods to handle missing data {20c}

For missing data imputation, the last observation carried forward method will be used if the missing data met the following hypothesis: missing completely at random.

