### Eligibility criteria {10}

#### Participants

##### Inclusion criteria

According to the Kidney Disease: Improving Global Outcomes (KDIGO) guidelines, CKD refers to the abnormalities in the kidney structure or function or an estimated glomerular filtration rate (eGFR) of < 60 ml/min/1.73 m^2^ that persists for 3 months with or without kidney damage. The GFR was obtained by calculating the CKD-EPI using the following Cystatin C formula: eGFR=169 × Scr^-0.608^ × CysC^−0.63^ × Age^−0.157^ × (0.83 if female).Patients diagnosed with CKD stages 3–5 (non-dialysis dependent) aged 30–65 years (including those aged 30 and 65 years).Sex and ethnicity restrictions were not imposed.Patients without atherosclerosis in the common carotid artery as observed on the vascular ultrasound examination and no history of atherosclerosis in the carotid artery.An informed consent form from participants is required (Supplementary document).

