#### Criteria for modifying or discontinuing intervention {11b}

Participants (1) who cannot tolerate aspirin, (2) in whom treatment was discontinued for more than 2 months due to various reasons, and (3) who will voluntarily withdraw from the study. Those who chose to withdraw from the study will receive appropriate treatment based on the judgment of each central investigator.

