### Outcomes {12}

The primary outcome (see Table 1) is atherosclerosis at treatment endpoint (36 months).

**Table 1 Tab1:** Primary and secondary outcomes of the study

Outcome	Metric	Time point

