**Secondary**		
The combined cardiovascular events	Incidence	**36** months
All-cause mortality	Incidence	**36** months
eGFR decreased by 50%	the proportion of eGFR decreased by 50%	**36** months
Safety outcomes	Numbers	**36** months

Carotid ultrasonography will be used to screen for atherosclerosis. The bilateral carotid arteries will be analyzed by color Doppler ultrasound at a frequency of 10 MHz using a linear array transducer (Model Vinno 70; VINNO Technology (Suzhou) Co., Ltd., China) by an experienced sonographer. A smooth carotid artery is considered normal. An atherosclerotic plaque is defined as a focal structure encroaching into the arterial lumen by at least 0.5 mm or 50% of the surrounding intima-media thickness (IMT) value or with a thickness of > 1.5 mm, as measured from the media-adventitia interface to the intima-lumen interface [21]. Both atherosclerotic plaques and IMT are indicators of carotid atherosclerosis. The carotid ultrasonography will be performed at 6, 12, 24, and 36 months to identify the status of carotid atherosclerosis.

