### Sample size {14}

#### Sample size estimation

The sample was calculated as follows: $$ n=\frac{{\left({z}_{\alpha}\sqrt{2\overline{pq}}+{z}_{\beta}\sqrt{p1q1+p0q0}\right)}^2}{{\left(p1-p0\right)}^2} $$

In this study, p0 and p1 represent the estimated exposure rates of the control group and the experimental group, respectively, while *Z*_α_ and *Z*_β_ indicate the standard positive distribution boundaries. In the table, when *α* or *β* is equal to 0.05, its value is 1.96; when *α* or *β* is equal to 0.01, its value is 2.58. In this study, the incidence of p0 is above 40% [8]. After the intervention, p1 is expected to decrease by 15% compared with p0 (p1 = 25%). Let *α* = 0.05 (both sides), and *β* = 0.10. The calculated minimum sample size is 251; if 10% of the cases were lost to follow-up, the calculated sample size would be 277 for each group, and approximately 554 patients will be included in the trial.

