### Statistical analysis

#### Statistical methods for primary and secondary outcomes {20a}

For the primary outcome, the chi-square test will be performed to compare the occurrence rate of atherosclerosis at 1, 2, and 3 years of follow-up between the aspirin group and the placebo group. For the secondary outcome, the chi-square test will be performed to compare the combined cardiovascular events and all-cause mortality at 1, 2, and 3 years of follow-up between the aspirin group and the placebo group. Then, the decrease in eGFR will be computed using the value measured at the last follow-up minus the value measured at baseline; patients with a 50% decline in eGFR will be treated as patients who experienced an eGFR reduction of 50%. Similarly, the proportion of patients with an eGFR reduction of 50% between the aspirin group and the placebo group will be compared using the chi-square test. If the previous comparison did not reach a significant difference, the magnitude of decrease in eGFR between the two groups would be compared using two independent sample *t* tests or the Mann-Whitney *U* tests. In addition, multivariate competing-risk regression models will be used to assess the independent effect of treatments adjusted for age, sex, diabetes, serum lipid profiles, and phosphorus.

All statistical analyses will be performed using the SPSS software version 21.0 (IBM Corp., Armonk, NY, USA), and general data will be expressed as mean ± standard deviation. The variables with normal distribution and variance will be compared. One-way analysis of variance will be used for comparisons within groups. The SNK test will be used for multiple comparisons between groups. Pearson’s correlation analysis will be used for analyzing the correlation between variables. A nonparametric test will be used to analyze variables that do not meet the parameter test conditions. The Kruskal-Wallis *H* test or Mann-Whitney *U* test will be used for data comparison. Spearman’s correlation analysis will be used for correlation analysis. The chi-square test will be used for comparison. A *p* value of < 0.05 will be considered significant. A nonparametric test for multiple comparisons will be corrected using the Bonferroni method, *p* < 0.008, statistically significant safety analysis.

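### Last observation carried forward understates 36-month atherosclerosis even when data are missing completely at random, and it biases the comparison if loss differs by arm

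*Protocol article*

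**What the plan says.** All references are to the protocol article.

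- **Missing data** (section {20c}): "the last observation carried forward method will be used if the missing data met the following hypothesis: missing completely at random". No other imputation rule is given.
- **Entry state** (Inclusion criteria): the trial takes "Patients without atherosclerosis in the common carotid artery as observed on the vascular ultrasound examination", with no history of carotid atherosclerosis.
- **Endpoint and scans** (Outcomes {12}): the primary outcome is binary, atherosclerosis at 36 months. "The carotid ultrasonography will be performed at 6, 12, 24, and 36 months".
- **Test** (section {20a}): "the chi-square test will be performed to compare the occurrence rate of atherosclerosis at 1, 2, and 3 years of follow-up". The same section adds competing-risk regression, adjusted for age, sex, diabetes, lipids and phosphorus.
- **Analysis set** (section {20b}): the efficacy analysis is called intention-to-treat, "which will be conducted in all patients who have been randomized and used drugs".
- **Routes off treatment** (section {11b}): patients "who cannot tolerate aspirin, (2) in whom treatment was discontinued for more than 2 months due to various reasons", listed next to voluntary withdrawal.
- **Planned loss** (Sample size {14}): 10%, not split by arm.

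**The concern.** LOCF is neutral only if a patient's status would not have changed after the last scan. Here every patient starts plaque-free, and the endpoint is new onset, which accumulates up to month 36. A patient who leaves after a clear month-6 scan is analysed as clear at month 36, although some such patients would have developed plaque in the next 30 months.

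MCAR does not repair this. Under MCAR the patients who stay are a fair sample of all patients, so their 36-month rate is already unbiased. LOCF then adds a bias that was not there. The condition attached to the method is therefore not one that makes it valid.

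Two things are at stake. The 36-month rate in each arm is too low, which dilutes a real difference. If the arms lose different numbers of patients, or lose them at different times, the understatement is unequal and appears as a treatment effect in the primary test.

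**Working it through.** The plan gives no figure for the effect of LOCF, so there is none to reproduce. Its sample-size figures serve as inputs. (The printed formula gives 251 per group at β = 0.05 and 203 at the stated β = 0.10. That is a separate question, and only the planned 277 per group is used here.)

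**Inputs from the protocol:** 40% placebo and 25% aspirin at 36 months, two-sided 5% test, 277 per group, 10% loss overall, scans at 6, 12, 24 and 36 months, plaque-free at entry.

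**Assumptions not in the protocol:** constant onset hazard; dropout independent of onset within each arm; the timing of dropout; the split of loss by arm.

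**1. Onset over time at 40%.** λ = −ln(0.60)/36 = 0.01419 per month, and F(t) = 1 − exp(−λt). This gives F(6) = 0.0816, F(12) = 0.1566, F(24) = 0.2886, F(36) = 0.40.

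**2. Share of dropouts carried as events.** With dropout uniform over 36 months, the carried scan is baseline (weight 6/36), month 6 (6/36), month 12 (12/36) or month 24 (12/36):

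m = 0 + 0.0136 + 0.0522 + 0.0962 = 0.162.

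If all leave before month 6, m = 0. If all leave after month 24, m = 0.289. The true value is 0.40 in every case.

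**3. LOCF rate.** With loss d, the rate is (1 − d) × 0.40 + d × m. At d = 0.10 it is 0.360 + 0.0162 = 37.6%, or 2.4 points too low.

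**4. Equal loss, true 40% v 25%.** For 25%, λ = −ln(0.75)/36 = 0.00799 and the same weights give m = 0.0965. At 10% loss the LOCF rates are 37.6% and 0.225 + 0.0096 = 23.5%, so the difference is 14.2 points instead of 15. At 20% loss it is 13.3 points.

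**5. Unequal loss, no true effect (40% v 40%).** False benefit = (d_aspirin − d_placebo) × (0.40 − m). For 15% v 5% with uniform dropout this is 0.10 × 0.238 = 2.4 points (36.4% v 38.8%). The standard error is √(2 × 0.376 × 0.624/277) = 0.0412, so the mean z is 0.58. The rejection rate is 0.083 in favour of aspirin plus 0.006 against it, which is 0.089.

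| Loss, aspirin v placebo | Timing | False aspirin benefit (points) | Type I error |
|---|---|---|---|
| 10% v 10% | any | 0 | 5.0% |
| 15% v 5% | uniform | 2.4 | 8.9% |
| 15% v 5% | all before month 6 | 4.0 | 16.5% |
| 15% v 5% | all after month 24 | 1.1 | 5.8% |
| 25% v 10% | uniform | 3.6 | 14.1% |
| 10% v 20% | uniform | −2.4 | 9.0% |

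**6. Check by simulation** (5,000 trials per scenario, uniform dropout). For 15% v 5% with no true effect, LOCF gave a false benefit of 2.4 points and 8.3% rejections. Analysing completers only, in the same trials, gave a bias below 0.1 point and 4.8% rejections. Under this dropout the bias comes from LOCF, not from the loss itself.

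**The case against.** The strongest reply is that the rule applies only under MCAR. Read strictly, MCAR excludes loss that depends on arm, so the unequal-loss rows of the table lie outside the rule. Within it, the error is about one point towards no difference and type I error is 5%. Power barely moves: in simulation at 10% equal loss it was 95.2% with LOCF and 94.9% with completers. This limits the size of the point. It does not rescue the method, because the estimated rates are still wrong under exactly the condition named. Observed data can contradict MCAR but cannot establish it, so LOCF may be applied when loss does differ by arm.

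A reader might also infer several stronger things that the documents do not support:

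- *Every dropout is counted as event-free.* No. A patient with plaque on an earlier scan is carried as an event, about 16% of dropouts under uniform loss.
- *Aspirin will look falsely better.* This needs more, or earlier, loss on aspirin. The protocol gives no loss by arm. Section {11b} names aspirin intolerance, a possible arm-linked route, but does not say that such patients stop being scanned.
- *The dosed-only set adds to the bias.* It is a modified intention-to-treat set under the wrong label. If blinding holds, no bias from it is shown. The words open (Trial design {8}) and double-blind (section {17a}) conflict, but that is a separate matter.
- *Deaths become plaque-free, and intermediate scans are ignored.* Nothing says that deaths are imputed, and section {20a} tests at 1 and 2 years as well as 3.

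**Conclusion.** The point holds in a limited form. LOCF is the wrong method for a new-onset endpoint in patients free of the condition at entry, and MCAR does not justify it. It understates the 36-month rate by freezing as event-free each dropout who was plaque-free at the last scan.

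With equal 10% loss the cost is dilution of a 15-point difference to about 14 points, with no excess false positives. With the same overall loss split 15% v 5%, the arm with more loss gains a false 2.4 points and type I error rises to about 9%, ranging from 5.8% for late loss to 16.5% for early loss. The direction follows the loss and can run against aspirin. These figures rest on a constant hazard, dropout independent of onset, and assumed arm splits and timing. The understatement itself needs only that some patients who are plaque-free at their last scan would develop plaque afterwards.

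**What to change.** 1. Delete LOCF for the primary endpoint.
2. Estimate the 36-month risk of first atherosclerosis by arm, and the risk difference with a 95% confidence interval, from a discrete-time or interval-censored analysis of the 6-, 12-, 24- and 36-month scans. Each patient contributes up to the last scan. Treat death as a competing event, in line with the competing-risk models already named in section {20a}.
3. As sensitivity analyses, use multiple imputation and a tipping-point analysis that shows how far dropouts would have to differ from completers to change the conclusion.
4. Analyse all randomised patients as randomised, or rename the section {20b} set modified intention-to-treat.

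The cost is analysis wording and some programming, with no new data: the scans are already scheduled. The downside is a model-based primary estimate in place of a simple chi-square test. The chi-square test on patients with a 36-month scan can be kept as a supporting analysis.

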### Oversight and monitoring

#### Composition of the coordinating center and trial steering committee {5d}

Not available.

#### Composition of the data monitoring committee, its role, and reporting structure {21a}

##### Data and safety monitoring board

An independent Data Safety Monitoring Board (DSMB) has been established to maintain the oversight of patient safety and data integrity within the trial. The DSMB consisted of six members: three expert nephrologists (1 of them assigned as the head nephrologist), an ethicist, a biostatistician, and a patient representative. The DSMB has no financial, proprietary, professional, or other interests that may affect the impartial and independent decision-making in the trial. The DSMB will monitor the trial data. The safety, effectiveness, and integrity of the trial will be ensured.

##### Description of any interim analyses and stopping guidelines {21b}

The DSMB will evaluate the progress of participant recruitment and make recommendations to the sponsor to continue, modify, or terminate or suspend the trial in one or all groups as originally planned. The committee will meet in person or conduct an online conference prior to the trial commencement and then 3 and 6 months after the initiation of the trial. The DSMB will participate in the blinded interim analyses.

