### Participant timeline {13}

The time schedule of enrollment, intervention assessments, and frequency of visits of all participants are shown in a schematic diagram (see the Research flow chart). The participants will be followed up at 0.5, 1, 2, 3, 4, 5, 6, 12, 24, and 36 months.

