### Methods: assignment of interventions

#### Sequence generation {16a}

Central randomization will be used as a randomization method, and the random number will be generated and assigned by the designated data management center. We will use simple randomization for random allocations. Eligible patients will be randomly assigned to the aspirin group or the placebo group. The treatment will last for 36 months.

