### Assignment of interventions: blinding

#### Who will be blinded {17a}

The study is a double-blind study. The included patients will not be informed about the group to which they belong. The investigators in each center will not know which patients receive active drug or inactive drug.

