#### Procedure for unblinding if needed {17b}

If no pregnancy or other emergency occurs during the research period, the blinded participants will be unblinded according to the standard procedure when serious adverse events occurs. If the drugs used in the study have an impact on the treatment, emergency unblinding will be considered.

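### The listed DSMB meetings end at month 6 of a 36-month trial, and the two sections under item {21b} disagree on whether there are interim analyses

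*Protocol article*

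**What the plan says.** All references are to the protocol article.

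- **DSMB calendar.** Description of any interim analyses and stopping guidelines {21b} has the board meet, in person or online, "prior to the trial commencement and then 3 and 6 months after the initiation of the trial". It gives no interval and no continuing frequency after month 6.
- **DSMB data look.** The same section says "The DSMB will participate in the blinded interim analyses". It also lets the board recommend continuing, changing, suspending or ending the trial, for one group or for all.
- **Interim analyses.** The section Interim analyses, which carries the same item number {21b}, reads in full "Not applicable".
- **DSMB remit.** Data and safety monitoring board says "The DSMB will monitor the trial data", with no dates.
- **Duration.** Sequence generation {16a}: "The treatment will last for 36 months". Participant timeline {13}: "The participants will be followed up at 0.5, 1, 2, 3, 4, 5, 6, 12, 24, and 36 months".
- **Blinding.** Who will be blinded {17a}: "The investigators in each center will not know which patients receive active drug or inactive drug". For single cases, Procedure for unblinding if needed {17b} says "the blinded participants will be unblinded according to the standard procedure when serious adverse events occurs".
- **Known risk.** The Discussion reports that, in CKD, some studies suggest aspirin at 100 mg/day may increase cardiovascular disease and CKD progression. Intervention description {11a} gives 100 mg daily as the trial dose.

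**The concern.** The printed calendar covers the start-up phase and then stops. The visits at months 12, 24 and 36 all come after the last listed meeting. The harms named in the Discussion, cardiovascular events and loss of kidney function, accumulate over years, so most of the evidence on them would arrive when no review is listed.

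Blinded site investigators can recognise and treat an event in one patient, but they cannot see that events are more frequent in one arm. The DSMB is the only body that the article describes as independent and responsible for patient safety, so its calendar matters.

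The two {21b} sections also leave open whether the board looks at accumulating data at all and, if it does, whether the data are pooled or split by arm. A board that may recommend stopping one group needs data split by arm.

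**Working it through.** The plan gives no figure to reproduce. The check is arithmetic on the calendar, followed by a comparison of the two sections.

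**Inputs.** 554 patients and 10% loss (Sample size {14}); 36 months of treatment (Sequence generation {16a}); last listed meeting at month 6 (Description of any interim analyses and stopping guidelines {21b}); first assignment on 1 March 2020 and recruitment complete by March 2020 (Trial status). Assumption: the trial is initiated when the first participant is assigned.

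**Calendar gap.** 36 − 6 = 30 months; 30/36 = 83%.

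**Exposure after the last listed meeting**

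| Scenario | Total patient-years | By month 6 | After month 6 |
|---|---|---|---|
| All start on day 1, no loss | 554 × 3 = 1,662 | 554 × 0.5 = 277 | 1,385 (83.3%) |
| Day-1 start, 10% loss spread evenly over 36 months | 554 × (3 − 0.15) = 1,578.9 | 554 × (6 − 0.05)/12 = 274.7 | 1,304.2 (82.6%) |
| Uniform recruitment over one month, no loss | 1,662 | 554 × 5.5/12 = 253.9 | 1,408.1 (84.7%) |

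In the second row, a patient who is lost misses on average 18 of 36 months, so the mean loss is 0.10 × 1.5 = 0.15 years. Over the first 6 months the mean loss is 0.10 × 6²/(2 × 36) = 0.05 months.

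If uniform accrual took 6, 12 or 24 months (assumed), the share of planned exposure accrued by month 6 would be 8.3%, 4.2% or 2.1%. The uncovered share would then be 91.7%, 95.8% or 97.9%. These rows all restate the same calendar gap in patient-years. They measure exposure, not expected harm.

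**Effect of later meetings (day-1 start, no loss)**

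- Last meeting at month 24: 554 × 1 = 554 patient-years remain (33.3%). With meetings at months 12 and 24 the longest gap is 12 months.
- Last meeting at month 30: 554 × 0.5 = 277 remain (16.7%). With one-month recruitment it is 1,662 − 554 × 29.5/12 = 300.1 (18.1%). With meetings every 6 months the longest gap is 6 months.

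**The two {21b} sections side by side.** One says interim analyses do not apply. The other says they take place, are blinded, and involve the DSMB. If blinded means pooled over arms, the board cannot tell which group to stop, so its power to recommend stopping one group has no data behind it. If blinded means arms under coded labels, the board can compare groups, but that is a comparative look at accumulating data and sits badly with the other section. Neither section says which is meant. No effect on type I error can be computed, because the number, timing and content of the looks are not given.

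**The case against.** The strongest reply is that the list of meetings is not said to be complete. The board's remit has no end date, Trial status sends it any protocol amendments, and a full calendar often sits in a charter that a journal article omits. This stands in part. A reader might infer that independent review ends at month 6, and the documents do not say that. They show only that no later meeting is listed. The point survives because it does not rest on silence: the article chose to print specific dates, and those dates stop.

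A second reply is that late harm is not unguarded. Adverse event reporting and harms {22} keeps surveillance going throughout treatment and follow-up, serious events can lead to individual unblinding, and Safety outcomes calls for a halt after a treatment-related death at any time. That is correct, but these safeguards work case by case and do not compare rates between arms.

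A third reply is that the {21b} conflict has a mild reading: no formal efficacy analysis, plus a blinded data review. That may be what was intended, but the article does not say so, and the reading does not explain how one group could be stopped.

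A reader might also infer that the authority to stop is split, because the adverse event section lets investigators decide on termination and Safety outcomes sends a treatment-related death to the ethics committee without naming the DSMB. The documents do not support this. The adverse event text ties the decision to a safety visit and to the patient's condition, so it most naturally means ending one person's participation. Not naming the DSMB after a death is an omission, not a contradiction.

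**Conclusion.** The point holds in limited form. As printed, 30 of 36 months have no listed DSMB review, which is 83% of planned patient-years under a day-1 start, 83% with the planned loss and 85% with one-month recruitment. Slower accrual would raise the share. This rests on reading the listed meetings as the plan, on taking initiation as first assignment, and on treating the trial as double-blind as its blinding section states (Trial design {8} calls it open, which is a separate matter). The {21b} inconsistency is real on the face of the text.

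This is an oversight defect that should be corrected before recruitment. It does not invalidate the primary analysis, and it shows neither that harm will be missed nor that the type I error is inflated.

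**What to change.** **In Description of any interim analyses and stopping guidelines {21b}:**

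- State that after month 6 the existing DSMB continues to meet at regular intervals until the last participant completes treatment. Every 6 months is one reasonable choice. The minimum is a meeting around each of the month 12 and month 24 visits, when new laboratory and ultrasound data arrive. Meetings at months 18 and 30 would rest mainly on adverse event reports.
- State that at each meeting the board reviews a closed report by coded arm on bleeding, serious adverse events, deaths, cardiovascular events and eGFR decline. The last two are the risks that the Discussion names.
- State that the review is for safety only and includes no test of the primary endpoint. Deaths, cardiovascular events and 50% eGFR decline are also secondary endpoints, so say plainly that they are reviewed for harm and that no early claim of benefit can follow.
- Replace the sentence on blinded interim analyses with this text. The section Interim analyses {21b} can then stand as it is, and no alpha is spent.

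An optional addition under Safety outcomes is to notify the DSMB, as well as the ethics committee, of a treatment-related death.

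**Cost.** Two to four more online meetings of a board that already exists (more if recruitment overruns), a closed safety report for each, prepared by someone outside the blinded site teams, and a change of wording. Sample size, visit schedule and primary analysis are untouched.
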